### Randomisation

EQUIP-ACS has a cluster-randomised study design. Randomisation will be stratified by country and ability to perform percutaneous coronary intervention on-site. Centres will be randomised to the QI programme or not. The co-ordinating centre (CTEU) will inform centres at the beginning of the baseline phase of their randomised allocation. The rationale for this is that personnel at centres allocated to the QI training programme will require sufficient notification to ensure availability and secure travel arrangements for the meetings. There is a possibility that knowledge of the randomised allocation may influence practice patterns. However the influence of this potential bias can be tested by comparing treatment patterns across the two groups during the baseline data collection phase.

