### Sample size and statistical considerations

The primary outcome is based on the 8 quality improvement variables. Two of the variables will be available in all patients (risk stratification and statin use) whereas the others will be available in a proportion of the whole group. We can document the use of treatments as a proportion at a centre level or at the level of the patient we can score each variable as 1 (administered) or 0 (not administered), allowing a maximum score of 8 for each patient. For the sample size calculation it appeared more straightforward to use the scoring system. Some patients will not contribute to the final analysis as they may not be considered for 5 of the outcome measures. Using a pragmatic assumption we estimate that the average "maximum" score per patient will be 5, allowing for the fact that a proportion will not contribute to the final analysis. To calculate the sample size we have taken the possible differences in score using simulated individual level patient data corrected for centre effect (i.e. that patterns of practice in a particular centre will have similarities across patients treated at that centre and therefore results from each patient cannot be regarded as "independent"). If the maximum score is estimated at 5 each one point would equate approximately to a 20% absolute difference in the frequency of use of that treatment at a centre level. We estimate that a 10% absolute difference would be considered reasonable "minimum" difference to demonstrate that the QI programme can change practice. This equates to an absolute average difference of about 0.5 between the QI centres and control.

In PROMIS-UK [31] we found that a difference of 0.3 between the education group and control group was just detectable with a p value of 0.05, with a total of 1000 patients and 38 centres. The inter-cluster correlation coefficient (ICC) for the control arm of PROMIS was 0.10026.

The sample size estimate for EQUIP uses the following formula:(1)

Where "N_cluster_" and "N_simple_" are the sample sizes for cluster randomisation and simple randomisation respectively. "m" is the number of patients per cluster (i.e. per hospital) and "ICC" is the inter-cluster correlation coefficient.

The table below shows the detectable differences in scores between groups using an ICC of 0.1 or 0.2 and 40 or 50 patients per centre.

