Table 1 shows that the study is well powered in the post QI phase to detect differences of about 0.4 with 800 patients assuming an ICC of 0.2. Our anticipated total enrolment over the whole period (baseline, during the QI phase and post QI phase is expected to be a minimum of 2000 and a maximum of 4000, We believe the main "power" of the study will lie in the post QI phase and a total enrolment of 1000 patients (500 per group) will give us good power to detect differences of 0.3-0.4 which equates to absolute differences in rates of use of treatments of 6-8%, Since our minimum clinically important difference is 10%, the study can be considered "well powered". Centres will be asked to recruit all non-ST elevation ACS patients but we do not know the exact enrolment rate in the centres that will take part hence the need to identify a range of sample size estimations. However as this is largely driven by the number of centres it is important we have 40 participating centres.

**Table 1 T1:** Sample size calculation based on score of drug use at discharge

ICC	Centres per Group	Patients per Centre	Patients per Group	SD	Detectable Difference
0.1	20	20	400	0.9	0.312
0.1	20	25	500	0.9	0.302
0.1	20	30	600	0.9	0.295
0.1	20	40	800	0.9	0.286
0.1	20	50	1,000	0.9	0.281
					
0.2	20	20	400	0.9	0.401
0.2	20	25	500	0.9	0.394
0.2	20	30	600	0.9	0.390
0.2	20	40	800	0.9	0.384
0.2	20	50	1,000	0.9	0.380

It was not felt appropriate to use the estimated differences between baseline data and post QI data in the sample size estimation as too many assumptions needed to be made. Therefore we feel we have made a "conservative" sample size estimation that should allow a good opportunity to detect realistic differences between the two groups.

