### Statistical analysis plan

The primary outcome is a composite of 8 outcome measures. The proportion of outcomes fulfilled will be calculated on all patients for each time period and group. The change in the proportion over time (Δ = post QI - baseline) will be compared between groups.

Analysis of the primary outcome will be by hierarchical logistic regression to take account of the clustered nature of the data. For each patient up to 8 binary quality indicators will be recorded. The quality indicators are therefore nested within patient. Patients, in turn, are nested within centre. A three-level random effects model will be fitted with random effects for patient and centre. An indicator variable for time period (0 = baseline phase, 1 = post-QI phase) will be entered at level 2 (patient) as a fixed effect and an indicator variable for treatment group (0 = control, 1 = intervention) will be entered as a fixed effect at level 3 (centre). Other centre-level covariates that will be entered as fixed effects at level 3 are country and ability to perform PCI on site (since these will be stratification factors in the randomisation). The interaction between treatment indicator and time period will give a P-value and an estimate of the treatment effect expressed as an odds ratio for the probability of a quality indicator being fulfilled.

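### Country and on-site PCI enter only as centre-level main effects, so the adjustment for the stratification factors barely reaches the group-by-period interaction that is tested

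*Protocol article*

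**What the plan says.** The Randomisation section states: "Randomisation will be stratified by country and ability to perform percutaneous coronary intervention on-site".

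The Statistical analysis plan section writes the primary model out in some detail:

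- Random part: "A three-level random effects model will be fitted with random effects for patient and centre".
- Period: "An indicator variable for time period (0 = baseline phase, 1 = post-QI phase) will be entered at level 2 (patient) as a fixed effect".
- Stratification factors: "Other centre-level covariates that will be entered as fixed effects at level 3 are country and ability to perform PCI on site". The reason given is "since these will be stratification factors in the randomisation".
- Primary result: "The interaction between treatment indicator and time period will give a P-value and an estimate of the treatment effect expressed as an odds ratio".

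No product of country or PCI status with period is listed, and the random effects are for patient and centre only. The same section defines the comparison as the post-QI minus baseline change, set against each other between groups.

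**The concern.** Stratification factors are put into the primary model so that the tested effect is analysed in line with how centres were allocated. Here the factors are attached to the level of performance, while the test concerns the change in performance. A country that performs better throughout, or a PCI centre that performs better throughout, contributes the same amount in both periods and drops out. What could still matter for a change is a trend that differs by country or by PCI capability, and the model has no term for that.

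Such trends are plausible in this setting. The Background says that use of these treatments tends to rise over time in any case, and that limited resources such as revascularisation capacity can block improvement. Early angiography is one of the eight indicators. At stake are the size of the primary test and its power, though both only modestly.

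**Working it through.** **1. The protocol's own figure.** Table 1, first row: ICC 0.1, 20 centres per group, 20 patients per centre, 400 per group, SD 0.9, detectable difference 0.312. With two-sided 5% and 80% power (inferred, since the text does not state them for the table) and 38 df:

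(2.024 + 0.851) × 0.9 × √(2 × [1 + 19 × 0.1] / 400) = 2.875 × 0.9 × 0.1204 = 0.312.

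All ten rows reproduce in this way. The table concerns a single post-QI comparison of scores, so it neither supports nor contradicts the present point.

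**2. Why the main effects cancel.** On the linear predictor, for centre j in period t (0 or 1):

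η = α + country + PCI + β₁·group + β₂·t + β₃·group·t + u_j.

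Subtracting t = 0 from t = 1 within a centre leaves β₂ + β₃·group. Country, PCI and u_j are gone. If trends differ by country or PCI, the change becomes β₂ + β₃·group + (country trend) + (PCI trend), and the planned model has nothing to absorb the last two terms.

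**3. Check in the planned model.** The cancellation is exact only for a balanced linear model, so the three-level logistic model was simulated and fitted by maximum likelihood, 200 runs per scenario. From the documents: 5 countries, the PCI stratum, 40 centres and 25 patients per centre in the post-QI period (1000/40); the same number was used at baseline. Assumed, because the documents give no values: centre SD 0.5, patient SD 0.5, country effects from -0.6 to 0.6, PCI effect 0.4 (all logit), and 3 to 7 indicators per patient. Three fits: (a) no country or PCI, (b) main effects as in the protocol, (c) country and PCI by period added.

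| Scenario | (a) | (b) | (c) |
|---|---|---|---|
| Equal sizes, effect 0.4: SE | 0.1115 | 0.1115 | 0.1116 |
| Unequal sizes, effect 0.4: SE | 0.120 | 0.120 | 0.122 |
| Unequal sizes, effect 0.4: power | 92.5% | 92% | 92% |
| Null, country trends -0.4 to 0.4: type I error | 6.5% | 6.5% | 4.5% |
| Null, centre-specific trends SD 0.3 only: type I error | 13.5% | 14.5% | 13.5% |
| Null, both kinds of trend: type I error | 12.5% | 13.5% | 10% |

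Moving from (a) to (b) shifts the estimate by 0.001 on average (maximum 0.003) with equal sizes, and by 0.010 (maximum 0.043, about 0.36 SE) with unequal sizes. The Monte Carlo error of a 5% rejection rate is √(0.05 × 0.95 / 200) = 1.5 points, so 6.5% against 4.5% does not settle the matter by itself.

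**4. Centre-level check of type I error.** With 38 centres of unequal size, stratified allocation and country trends up to ±0.4 logit, the test without strata-by-period terms rejects in about 6-9% of null trials, against 5% with them. The terms cost about 2.5% in SE. The excess arises because allocation balances the number of centres per stratum, not the patients, and about 38 centres over 10 strata leave some strata uneven.

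**5. If a centre-by-period random effect is used.** Work per centre, with 20 centres per group:

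- Sampling variance of a centre's change: 0.1115² × 20/2 = 0.1243.
- Centre-specific trend variance (assumed SD 0.3): 0.09.
- Country trend variance for -0.4, -0.2, 0, 0.2, 0.4: (0.16 + 0.04 + 0 + 0.04 + 0.16)/5 = 0.08.

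SE without strata-by-period terms: √(2 × 0.2943/20) = 0.172. SE with them: √(2 × 0.2143/20) = 0.146. The second is also close to the true variability, because balanced allocation has already removed the country trends from the contrast. The first is therefore too large by a factor of 1.17. Simulation of this case (4,000 runs) gave 0.172 and 0.145, type I error 2.2% and 5.0%, and power for a log odds ratio of 0.4 of 62% and 74%.

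With trends half as large, the SE is 0.152 against 0.145 and power 72% against 75%. With no country trend, power is 76% either way. In the 38-centre check with unequal sizes, omission gave type I error of about 2-4% and an SE about 7-23% larger.

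**The case against.** The case on the other side is substantial, and much of it stands.

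- A reader might infer that the main effects cannot move the primary estimate at all. That is not supported: with a logit link and unequal centres they move it slightly, and the sample size section says enrolment rates are not known in advance.
- A reader might infer that the primary test ignores the stratification. The text contradicts this. Both factors are in the model for that very reason, and stratified allocation balances most of any country or PCI trend between groups with no model term. What remains is chance imbalance, not systematic bias.
- A reader might infer a large loss of precision. Regressing centre-level changes in a constructed example can show one (SE 0.120 falling to 0.088 on adjustment), but that is not the planned analysis and the trends in it are invented. In the model as written, adding the terms gave no gain in SE or power.
- The Background remark on rising use concerns an overall trend and the weakness of historical controls. Concurrent controls and the period term deal with that. No passage says that trends differ by country or PCI status, so their size is an assumption.
- The larger inflation in the simulations, about 14%, comes from centre-specific trends. The strata-by-period terms leave it at 13.5%. That is a separate issue and should not lend weight to this one.

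None of this removes the narrower point: the adjustment as specified hardly acts on the contrast it is meant to serve.

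**Conclusion.** The point holds in a limited form. The cancellation follows from the model as written and needs no assumed values. Its consequence is modest and depends on trend sizes that the document does not give. For country trends of 0.2 to 0.4 logit with unequal centre sizes, type I error is roughly 6-9% in the model as specified. Once between-centre variation in change is modelled, the direction reverses: the test becomes conservative and loses power, by 12 points (62% against 74%) at the largest trends assumed and 3 points (72% against 75%) at half that size. If no such trends exist, nothing is lost by the current wording. This is an inexpensive improvement to the primary model, not a flaw that invalidates it.

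**What to change.** Add country-by-period and PCI-by-period fixed effects to the primary model and keep the main effects. This is one line of wording. It uses five degrees of freedom (four for country, one for PCI) out of about 38, and makes the SE about 1-3% larger if there are no differential trends.

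Alternatively, make the primary analysis a baseline-adjusted comparison of the post-QI period. There the country and PCI main effects act directly on the tested contrast and are sufficient.

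Neither change replaces a centre-by-period random effect in the interaction model. That should be decided separately.

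### The primary model pools up to eight different indicators into one odds ratio with no indicator term, and its only specified estimate is not on the scale of the 10% target

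*Protocol article*

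**What the plan says.** The Statistical analysis plan section of the protocol article sets out the primary model term by term. The unit of observation is the indicator: "For each patient up to 8 binary quality indicators will be recorded". Indicators are nested in patients and patients in centres, and "A three-level random effects model will be fitted with random effects for patient and centre". Of the fixed effects, the section states that "An indicator variable for time period (0 = baseline phase, 1 = post-QI phase) will be entered at level 2 (patient) as a fixed effect", that treatment group enters at centre level, and that "Other centre-level covariates that will be entered as fixed effects at level 3 are country and ability to perform PCI on site". The group-by-period interaction supplies the P-value and "an estimate of the treatment effect expressed as an odds ratio for the probability of a quality indicator being fulfilled". No covariate at the indicator level is listed, fixed or random.

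Before describing the model, the same section says that the proportion of outcomes fulfilled will be calculated by period and group. "The change in the proportion over time" is then to be compared between groups, with no method or interval attached.

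Under Sample size and statistical considerations, "a 10% absolute difference would be considered reasonable" as the minimum worth showing. This is equated to about 0.5 on a score whose average maximum is taken as 5. That section also says that only risk stratification and statin use will be available in every patient. The Abstract (Methods/Design) adds that each of the eight measures will be compared between groups with allowance for clustering.

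**The concern.** A logistic model with only patient and centre random effects gives every indicator in a patient the same probability. The eight indicators are unlike things: a documented risk score within 24 hours, an invasive procedure within 72 hours, in-hospital drugs, and discharge drugs in selected subgroups. Nothing in the article supports equal odds across them.

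If the rates differ, two things follow. The single odds ratio averages over indicators and lies nearer to 1 than the effect within an indicator. And the indicators in a patient vary less around their own rates than a common-rate model expects, which pushes the estimated patient variance down, possibly to zero.

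The second issue is scale. The trial's target is 10 percentage points, but the only estimate and P-value that the plan fully specifies are on the odds-ratio scale. How large an odds ratio meets the target depends on the control rate.

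**Working it through.** **1. The plan's own figures.** Table 1 reproduces with (t[0.975, 38 df] + t[0.80, 38 df]) × SD × √(2(1 + (m − 1)ICC)/(20m)). Two-sided 5% and 80% power are inferred, as the article states neither for this trial. Row 1: (2.024 + 0.851) × 0.9 × √(2 × 2.9/400) = 0.312, as printed. All ten rows match. The target also agrees with itself: 0.5/5 = 10%. Neither result bears on the missing term, but they fix the target as an absolute difference.

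**2. Attenuation.** Let indicator k have baseline rate p_k and share w_k of all indicator observations. With a common within-indicator odds ratio c, the pooled rate moves from P0 = Σ w_k p_k to P1 = Σ w_k·expit(logit p_k + ln c). The pooled odds ratio is [P1/(1 − P1)] / [P0/(1 − P0)], and the share retained is ln(pooled OR)/ln c. All rates and eligibility shares below are assumptions. The order of indicators is risk score, angiography, anticoagulant, beta-blocker, statin, ACE inhibitor, clopidogrel load, clopidogrel at discharge.

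| Assumed rates | Pooled OR if c = 1.5 | Pooled OR if c = 2.0 | Log OR retained |
|---|---|---|---|
| 65-87% (.65 .70 .74 .78 .81 .83 .85 .87) | 1.48 | 1.96 | 97% |
| 50-95% (.50 .60 .70 .75 .80 .85 .90 .95) | 1.43 | 1.86 | 89-90% |
| 15-92% (.15 .55 .92 .80 .88 .70 .65 .75), 7.05 indicators per patient | 1.35 | 1.66 | 74% |
| 15-92%, eligibility rescaled to 5 per patient | 1.32 | 1.60 | 68% |
| 10-95% (.10 .55 .95 .85 .90 .70 .70 .85) | 1.30 | 1.55 | 63-64% |
| 5-97% (.05 .30 .50 .70 .80 .90 .95 .97) | 1.24 | 1.45 | 54% |

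Eligibility is 1, 1, 1, .35, 1, .7, 1, 1 (sum 7.05) in the third row and 1, .9, .95, .4, 1, .6, .95, .95 (sum 6.75) in the first, second, fifth and sixth. The fourth row keeps risk score and statin at 1 and multiplies the other six by 3/5.05 = 0.594, so that the total equals the protocol's average of 5. Example, third row: P0 = 0.662; at c = 1.5, P1 = 0.726 and the OR is 1.35; at c = 2.0, P1 = 0.766 and the OR is 1.66.

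**3. Patient variance.** For the third row, with e_k the eligibility, the variance of a patient's total given independent indicators is Σ e_k p_k(1 − p_k) = 1.17. The pooled model expects 7.05 × 0.662 × 0.338 = 1.58, so the true value is 26% lower. Setting 1 + (7.05 − 1)ρ = 1.58/1.17 gives ρ ≈ 0.06: a within-patient correlation up to about that size would be estimated as none.

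**4. Fitted models.** Three-level data were simulated with 120 centres, 25 patients per centre and period, centre and patient SD 0.5 on the logit scale, and true OR 2.0. The model was fitted by maximum likelihood with and without indicator terms, on one data set per spread, so the estimates carry sampling error.
- Rates 65-87%: OR 2.07 without, 2.14 with; patient SD 0.42 and 0.47.
- Rates 10-95%: OR 1.69 without, 2.34 with; patient SD 0.00 and 0.55.

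**5. Change in indicator mix.** With no true effect, the four spreads with eligibility sum 6.75 were used. Raising beta-blocker and ACE-inhibitor eligibility by 25% in one arm-period gives a pooled OR of 1.01-1.03. Cutting angiography eligibility by 20% gives 1.01-1.04.

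**6. Scale.** A gain from p to p + 0.10 has odds ratio [(p + 0.10)/(0.90 − p)] / [p/(1 − p)]: 1.50 at p = 50%, 1.71 at 70%, 2.25 at 80% and 3.35 at 85%.

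**7. One indicator alone.** If only risk-score documentation moves, from an assumed 15% to 65%, the patient score rises by 0.5. With 5 indicators per patient that is 0.5/5 = 10 points, the whole target; with 7.05 it is 7.1 points.

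**The case against.** The strongest reply has five parts.

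- **No rates are given.** A reader might infer that the indicators are known to differ greatly and that the result will be badly distorted. The article does not show this. With rates of 65-87% the loss is about 3% of the log odds ratio. This stands: the direction is certain if rates differ, but the size is not known.
- **It is largely another estimand.** The plan asks for the odds of an indicator being fulfilled, averaged over indicators, and an averaged odds ratio nearer to 1 is non-collapsibility. With no effect and an unchanged mix it stays at 1. This stands too: a reader might infer a false-positive problem, and there is none from this source. Shifts in mix matter little in the cases tried.
- **The absolute scale is planned.** A reader might conclude that the trial cannot be read against 10%. That goes too far, because the same section plans a comparison of changes in proportions. What remains is that this comparison carries no clustering adjustment or interval, while the odds ratio carries the P-value.
- **Single-measure gains would be visible.** A reader might infer that a gain confined to risk-score documentation would go unnoticed. The Abstract plans a comparison of each measure, which would reveal it. The composite odds ratio alone would not.
- **The article is condensed.** A fuller analysis plan may exist. But the article does not leave the model open: it lists the terms at patient and centre level and none at indicator level. The point concerns a stated model.

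It is also tempting to argue that the two scales can disagree in sign. Control 60% to 70% and intervention 75% to 83% gives −2 points but a ratio of odds ratios of 1.63/1.56 = 1.05. That needs a 15-point baseline imbalance in a stratified randomisation and has nothing to do with the missing term, so it does not support this point.

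**Conclusion.** The point holds in a limited form. The stated model assumes equal odds for up to eight different indicators within a patient. If their rates differ, its odds ratio understates the within-indicator effect and its patient variance is too small. Retention of the log odds ratio runs from about 97% to 54% over the spreads tried, and all of these rest on assumed rates and eligibility. The null comparison is unaffected, and changes in mix move the odds ratio only to about 1.01-1.04.

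The scale issue rests on the article's own target and plain arithmetic: no single odds ratio corresponds to 10 points. The planned change in proportions does correspond, but lacks the cluster-adjusted interval needed to judge it. The plan should be changed because the better model costs almost nothing, not because the planned one is shown to give a wrong answer.

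**What to change.** Add indicator to the primary model as a fixed effect (7 contrasts). This removes most of the attenuation but still yields an odds ratio. So, from the same model, also report the standardised difference between arms in the change in proportion, in percentage points with a cluster-adjusted 95% CI, beside the odds ratio, and state that this difference is what is read against 10%. Present the eight per-measure comparisons next to the composite, so that a gain confined to risk-score documentation can be seen.

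Indicator-by-period terms, a centre-by-indicator random effect and a composite without risk stratification are optional sensitivity analyses.

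The cost is a few sentences of analysis-plan wording and a few more parameters. No new data are needed, and little is lost if the indicator rates prove similar.
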